### Data monitoring and auditing

Study participants will be closely monitored in the ICU. Suspected harms of the study treatment will be reported directly to study investigators. Case report forms will also be used to record any suspected harms and clinically important differences between treatment and control groups, including patient mortality, length of ICU stay, ventilator-free days, and electrolyte abnormalities, which will be analyzed using the statistical methods outlined in Table 
2. Data monitoring and quality assurance of the study will be undertaken by the investigators. The local investigator (CH) will undertake responsibility for such duties.

Study participants may be withdrawn from the study early if there is suspicion of treatment harm by the team caring for the participant, such as an allergic reaction, worsening renal function, or worsening hypernatremia; or if consent for study therapy is withdrawn by the participant or surrogate decision maker at any time. Treating physicians cannot withdraw patients from the study, but can decide to withhold study treatment. Participants who withdraw consent to the study will be asked whether they are withdrawing from any or all of: (1) study treatment, (2) future data collection, or (3) primary outcome data collection.

Formal data monitoring will not be performed in this small pilot randomized controlled trial, owing to both its small sample size and the small risk the intervention poses to study participants. A formal data-monitoring committee will be created to oversee the larger follow-up trial, should this pilot study demonstrate feasibility.

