**Assessments**								
*Baseline variables*								
Demographics	×							
Past medical history	×							
Type of diagnosis on admission	×							
APACHE-2 score at randomization	×							
SOFA score at randomization	×							
Diagnosis of ARDS at randomization	×							
Time since hemodynamic stability	×							
Length of ICU stay at randomization	×							
*Laboratory results*								
Renal function tests			×	×	×	×	×	
Serum chemistry			×	×	×	×	×	
Serum albumin levels			×	×	×	×	×	
Serum total protein levels			×		×		×	
Colloid osmotic pressure			×		×		×	
Blood gas analysis			×	×	×	×	×	
Troponin I levels			×	×	×	×	×	
Serum lactate levels			×	×	×	×	×	
Complete blood count			×	×	×	×	×	
*Physiologic data*								
Vital signs			×	×	×	×	×	
Glasgow Coma Scale rating			×	×	×	×	×	
Weight			×	×	×	×	×	
Ventilator data			×	×	×	×	×	
Fluid intake and output			×	×	×	×	×	
Diuretic doses and timing			×	×	×	×	×	
*Clinical outcomes*								
Study treatment held?			×	×	×	×	×	
Need for dialysis?			×	×	×	×	×	×
Hypotension requiring fluids			×	×	×	×	×	
Hypotension requiring vasopressors			×	×	×	×	×	
Suspected infection?			×	×	×	×	×	
Intubation status			×	×	×	×	×	×
Date of transfer from ICU			×	×	×	×	×	×
Date of death			×	×	×	×	×	×

APACHE-2, Acute Physiology and Chronic Health Evaluation-2; ARDS, acute respiratory distress syndrome; ICU, intensive care unit; SOFA, Sepsis-related Organ Failure Assessment.

Alternatively, if a treating physician believes that a patient might qualify for the study, and is in urgent need of diuresis, the patient can be considered for deferred consent. To be eligible for deferred consent, patients or surrogate decision makers must have already given consent for administration of blood products. Patients will then be randomized to a study arm and diuretics administered. Study investigators will try to obtain consent from the surrogate decision maker within the next 48 hours. If the surrogate decision maker cannot be located, the patient will be withdrawn from the study. Similarly, if the surrogate decision maker declines participation in the study, the participant will be withdrawn from the study. The deferred consent process is only to be used if the need for diuresis is urgent, and the surrogate decision maker cannot be reached in a timely fashion.

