**Figure 2 F2:**
[figure not shown]
**Patient treatment and data collection protocol.** IV, intravenous.

The study treatment, either 100 ml of 25% albumin or 100 ml of saline placebo, will be administered as an infusion over 60 minutes, within 2 hours of the patient’s prescribed dose of furosemide. Clinicians will be encouraged to prescribe furosemide twice daily so as to facilitate the timely administration of study treatment prior to furosemide administration.

In the event of new or worsening acute kidney injury, hypotension requiring further boluses of intravenous fluids or vasopressor agents, or if the caregiving team decides that further diuresis is unnecessary, study treatment will be held as long as the caregiving team also holds the furosemide. If a patient’s serum albumin level remains greater than 35 g/l for two measurements greater than 24 hours apart, study treatment will likewise be held. Patients will be monitored for up to 72 hours from randomization and those patients who the caregiving team decide need further diuresis, and have serum albumin levels <35 g/l, will resume the study treatment to which they were assigned.

If the participant develops a suspected adverse reaction to either the albumin, placebo, or furosemide, or the patient leaves the ICU (is transferred to the ward, another institution, or dies) study treatment will be discontinued.

No further administration of colloid intravenous fluids (albumin or starch) will be permitted while the patient is receiving study treatment. In the event that blood product transfusion is required for low serum hemoglobin levels (as opposed to active bleeding with hemodynamic instability), one dose of the study treatment may be held and the prescribed furosemide may be given after the blood transfusion is completed, at the discretion of the caregiving team.

Nursing staff will be provided with a bedside schedule to ensure that the study drug is administered in a timely fashion and that necessary measurements are performed and blood samples collected. The short duration of treatment and the ease of study drug administration will facilitate adherence across both ICUs.

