### Statistical methods

All *P* values will be two sided, with a level of *P* ≤ 0.05 indicating statistical significance. All data will be analyzed using statistical software on an intention-to-treat basis. All randomized participants, regardless of protocol adherence, will be included in the main analysis.

Feasibility outcomes will be calculated as proportions with 95% confidence intervals, with feasibility being met if the lower-bound of the 95% confidence interval is above the level pre-specified for feasibility (Table 
3). Data regarding our primary and secondary clinical outcomes will also be collected during this pilot study for future analysis; however, no analysis of clinical outcomes will be made for this pilot study, as the main purpose is to inform the definitive trial. Data collected from this pilot study will remain blinded and eventually incorporated into the dataset for the definitive trial, with the following pre-specified analyses.

Comparisons between the two treatment groups at a single time point (for example, baseline variables, number of patients requiring fluid bolus or vasopressors for hypotension, total dose of furosemide, and so on) will made using unpaired Student’s *t* test. Comparisons within a treatment group at different time points (change in serum albumin, colloid osmotic pressure, total protein, weight, fluid balance, oxygenation, lung compliance at day 3 and day 5, and so on) will be analyzed in a similar fashion. Multiple between-groups comparisons of continuous variables will be analyzed by repeated-measures analysis of variance. Linear regression will be used where appropriate to correct for baseline variables. Ventilator-free days will be defined as the number of 24-hour periods in which a patient does not need ventilation during 28 days (patients who die, by definition, will have 0 ventilator-free days). Survival analysis will be performed to assess 30-day mortality.

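### The protocol lets suspected harm lead to withdrawal from the study, which conflicts with its own treatment-only rules and leaves follow-up of those patients, and the counting of failed deferred consents, unsettled

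*Protocol article*

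**What the plan says.** All references are to the protocol article.

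- **Data monitoring and auditing, suspected harm.** "Study participants may be withdrawn from the study early if there is suspicion of treatment harm by the team caring for the participant". The examples are allergic reaction, worsening renal function and worsening hypernatremia.
- **Same paragraph, next sentence.** "Treating physicians cannot withdraw patients from the study, but can decide to withhold study treatment".
- **Same paragraph, data options.** "Participants who withdraw consent to the study will be asked whether they are withdrawing from any or all of" study treatment, future data collection or primary outcome data collection. The choice is described for consent withdrawal only.
- **Interventions.** "If the participant develops a suspected adverse reaction to either the albumin, placebo, or furosemide", study treatment is discontinued. For new or worsening acute kidney injury, study treatment is held while furosemide is held, and it may resume. Both rules concern treatment, not participation.
- **Recruitment plans and consent process, deferred consent.** Randomization comes first: "Patients will then be randomized to a study arm and diuretics administered". Consent is then sought within 48 hours. "If the surrogate decision maker cannot be located, the patient will be withdrawn from the study"; likewise, "if the surrogate decision maker declines participation in the study, the participant will be withdrawn from the study".
- **Statistical methods.** "All randomized participants, regardless of protocol adherence, will be included in the main analysis". A feasibility proportion passes only if its lower 95% bound exceeds the threshold.
- **Outcomes.** Adherence and completion of six doses are both defined on randomized patients; the completion threshold is 80%.

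**The concern.** Two questions are left open after randomization.

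The first is what happens to a patient in whom harm is suspected. One section speaks of leaving the study, the next sentence denies treating physicians that power, and Interventions only stops or holds treatment. If site staff act on the sentence that allows withdrawal, follow-up may end because of worsening renal function, in a trial that lists dialysis, ventilator-free days and mortality as outcomes. Missing data of that kind would be related to the outcome and could differ by arm. The trial has no formal data monitoring, so complete records on these patients matter more.

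The second is how a randomized patient counts when deferred consent fails. This is a consent matter and a different problem from the first. It bears on the pilot's primary outcome, because the feasibility proportions rest on about 50 patients.

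**Working it through.** **1. Suspected harm: the sections side by side**

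| Event | Interventions | Data monitoring and auditing |
|---|---|---|
| Allergic or other suspected adverse reaction | Study treatment discontinued | May be withdrawn from the study |
| Worsening renal function | Study treatment held, may resume | May be withdrawn from the study |
| Worsening hypernatremia | Not named | May be withdrawn from the study |
| Who may withdraw | Not addressed | Not treating physicians; nobody else is named |
| Data collection afterwards | Not addressed | Options given for consent withdrawal only |

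The intention-to-treat sentence covers departures from protocol adherence. It keeps these patients in the analysis set, but it does not say that their outcomes continue to be collected.

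**2. Where lost data would matter**

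Statistical methods plans no clinical-outcome analysis in the pilot and carries the data into the definitive trial. Dissemination policy has outcomes published by treatment group if the pilot proves non-feasible. Either route uses the data.

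**3. Deferred consent**

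Twice-daily dosing over 48 hours is 2 × 2 = 4 doses, so up to four of the six may have been given when consent fails. Such a patient cannot count as having completed six doses.

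**4. The plan's own figures**

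Table 3 follows n = z² p(1 − p)/d² with z = 1.96.

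- First-dose adherence: 3.8416 × 0.925 × 0.075 / 0.075² = 47.4 (stated 47).
- Completion: 3.8416 × 0.90 × 0.10 / 0.10² = 34.6 (stated 34).

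Both agree apart from rounding, so the plan's precision basis is the Wald interval. The target of 50 leaves 50 − 47 = 3 patients to spare.

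**5. What the denominator does to the completion criterion**

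The documents give no withdrawal or deferred-consent failure rate, so the counts below are assumptions. The Wald lower bound is L = p − 1.96 √(p(1 − p)/n). Withdrawn patients are either kept as non-completers or dropped.

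| Withdrawn | All randomized | L | Withdrawn dropped | L |
|---|---|---|---|---|
| 1 | 44/50 = 88.0% | 79.0%, fails | 44/49 = 89.8% | 81.3%, passes |
| 3 | 42/50 = 84.0% | 73.8%, fails | 42/47 = 89.4% | 80.5%, passes |
| 4 | 43/50 = 86.0% | 76.4%, fails | 43/46 = 93.5% | 86.3%, passes |

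First row in full:

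- 0.880 − 1.96 √(0.880 × 0.120/50) = 0.880 − 0.090 = 0.790
- 0.898 − 1.96 √(0.898 × 0.102/49) = 0.898 − 0.085 = 0.813

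The one-patient change at 44 completers is specific to the Wald interval. The Wilson bound, (p + z²/2n − z √(p(1 − p)/n + z²/4n²))/(1 + z²/n), gives 78.2% for 44/49, which still fails. The last row changes verdict under all three usual intervals (Wald, Wilson, exact): 76.4%, 73.8% and 73.3% for 43/50, against 86.3%, 82.5% and 82.1% for 43/46.

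First-dose adherence is less exposed, because the first dose would usually precede any withdrawal.

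**The case against.** The strongest reply is that the protocol already says enough. Outcomes defines completion on randomized patients, Statistical methods includes all of them, and no sentence removes a withdrawn patient from any denominator. The harm sentence is permissive and does not name the caring team as decision-maker; the next sentence can be read as limiting it. Suspected harms go onto case report forms, and Data collection says that ICU transfer, ventilator-free days and death are easily retrieved from hospital records. Deferred-consent withdrawal is a consent safeguard for urgent cases.

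Much of this stands. A reader might infer that the withdrawal rules remove randomized patients from the analysis, or flatly contradict intention-to-treat. The documents do not support that: they never equate withdrawal with exclusion, and the dropped columns above depart from the stated denominator. A reader might also infer a bias that makes albumin look safer. That requires withdrawals to concentrate in the albumin arm, whereas the protocol hypothesizes less kidney injury with albumin, so the imbalance could run the other way.

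What the reply leaves unanswered is follow-up. Being able to retrieve records is not a statement that data collection continues for a patient withdrawn from the study. The data options are given only for consent withdrawal, and the differing consequences for the same event in Interventions and in Data monitoring and auditing remain.

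**Conclusion.** The point holds as a conflict in wording with a real but conditional consequence. For suspected harm, the protocol does not settle whether the patient leaves the study or only has treatment stopped or held, and it does not say that data collection continues. Acting on the withdrawal wording could cause outcome-related loss of dialysis, ventilation and mortality data. The size and direction of that effect cannot be derived from the documents, and it would appear in the definitive trial or in the by-arm publication after non-feasibility.

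For failed deferred consent, the randomized-patient denominators are already stated and need only confirmation. The confirmation matters because, under assumed counts and Wald bounds, one patient separates failing (79.0%) from passing (81.3%) the completion criterion. The change is worth making before recruitment, which the article says has not begun.

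**What to change.** 1. Reconcile Interventions with Data monitoring and auditing so that suspected harm affects study-treatment status only. This point leaves every holding, resuming and stopping rule as it is; where the sections differ on what happens to treatment, the investigators must settle it.
2. State that data collection to day 30 continues for patients in whom harm is suspected, whatever their treatment status.
3. Reserve withdrawal from the study for consent decisions, with the tiered data options already described.
4. In the deferred-consent text, confirm that randomized patients whose consent fails stay in the randomized-patient feasibility denominators and are reported separately. Make any use of their clinical data subject to ethics-board approval.

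The cost is a wording change with a minor ethics amendment, and possibly slightly less favourable feasibility figures.

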### Research ethics approval and confidentiality

The study protocol, written and verbal consent forms, data to be collected, and recruitment posters have been approved by the Hamilton Integrated Research Ethics Board (Project #14-002). Any modifications of the protocol that might impact patient safety, confidentiality, or other significant conduct of the study will be reviewed by the Hamilton Integrated Research Ethics Board before implementation. Minor administrative changes will be reviewed by the investigative team but not the Hamilton Integrated Research Ethics Board.

All study information will be stored securely in locked cabinets or on secure, password-protected computer systems with limited access at the study sites. All case report form data, laboratory specimens, and administration forms will be identified with a coded identification number to maintain patient confidentiality. Records containing patient names and other identifying information will be stored in a separate locked area with limited access. No patient-identifying information will be published or released to anyone outside of the study team.

### Access to data

Data management will be performed by members of the Department of Epidemiology and Biostatistics at McMaster University. The study investigators will have full access to study datasets. External requests for study data will be granted, however any information that is shared will be blinded to any identifying participant information.

### Ancillary and post-trial care

Patients enrolled into the study will receive routine care from the intensive care team following completion of study treatment. Should this study, or its follow-up studies, provide evidence of the effectiveness, no further provision of treatment to participants will be required, as the study treatment is for short-term use only.

### Dissemination policy

There are no stipulations on publication in place by any party, including the trial sponsors. The study investigators will publish the results of the pilot study, including feasibility outcomes and characteristics of the study cohort, should feasibility be demonstrated. Outcomes analyzed by the treatment group will only be published if non-feasibility is demonstrated; otherwise pilot outcome data will be retained for incorporation in the larger follow-up study. Attempts will be made to accomplish publication within 6 months of trial completion, and in keeping with the CONSORT guidelines for randomized controlled trial publication
[22]. Authorship for publications will be in keeping with guidelines from the International Council of Medical Journal Editors
[23]. Following the completion of this pilot study, and the larger, follow-up study (should this pilot demonstrate feasibility) a completely de-identified data set will be archived for sharing purposes.

## Discussion

The FADE study is the first prospective randomized controlled trial to assess the use of hyperoncotic albumin in addition to diuretics in a general ICU population. Should this pilot study demonstrate feasibility, the primary outcome of the larger clinical trial will be an increase in the number of ventilator-free days, with secondary clinical outcomes of reductions in the duration of mechanical ventilation, length of ICU stay, episodes of hemodynamic instability, and mortality. The addition of 25% albumin to standard diuretic therapy is a promising treatment in the post-resuscitation care of critically ill patients with edema.

## Trial status

The trial is not yet recruiting.

## Abbreviations

APACHE: Acute physiology and chronic health evaluation; ARDS: Acute respiratory distress syndrome; CONSORT: Consolidated standards of reporting trials; FiO_2_: Fraction of inspired oxygen; ICU: Intensive care unit; PaO_2_: Partial pressure of oxygen in arterial blood; RIFLE: ‘Risk, injury, failure, loss, end-stage renal disease’; SaO_2_: Oxygen saturation; SOFA: Sepsis-related organ failure assessment.
